The major contents of Yirui capsule include perilla oil, *Folium Ginkgo* (Yinxingye), *Radix Salviae miltiorrhizae* (Danshen), *Fructus Crataegi* (Shanzha), *Rhizoma Alismatis* (Zexie), and *Radix Notoginseng* (Sanqi). A modern pharmacological study showed that the main functional component of Yirui capsules was alpha-linolenic acid [11]. Recent studies have illustrated that alpha-linolenic acid could improve vascular inflammation and endothelial function and be helpful in secondary prevention of CHD [12–14]. The lipid-lowering effect of other herbal components has also been illustrated in animal experiments [15–19]. Possible mechanisms may relate to limitation of absorption, promotion of the metabolism, and transformation of blood lipids. As a Chinese Herbal Medicine, Yirui capsules could help prevent the generation of hyperlipidemia and regulate the blood lipid level. Two animal experiments have been completed and demonstrated that Yirui capsules could significantly reduce the LDL-C level in hyperlipidemic rat models [20, 21]. Nevertheless, there is still a lack of high-quality evidence from clinical trials to support the application. In the current study, we aim to demonstrate and assess the efficacy and safety of Yirui capsules in improving hyperlipidemia by using a randomized controlled trial (RCT). We chose simulant Yirui capsules which contained only a placebo as a comparator so that the actual lipid-lowering effect of the Yirui capsules could be evaluated.

The study was financially supported by Infinitus (China) Company Limited and was registered with an identifier (ChiCTR-IOR-15006496, 29 May 2015) in the Chinese Clinical Trial Registry (ChiCTR). This funding source had no role in the design of this study and will not have any responsibility during its execution, analyses, interpretation of the data, or decision to submit results.

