### Statistical analysis

All effectiveness and safety evaluations will be conducted according to the intention-to-treat (ITT) principle. The last-observation-carried-forward method will be applied to deal with missing values. SAS (Version 9.2) will be utilized to analyze the data, and the statistical significance is defined as a two-sided *P* value of <0.05. For measurement data, the mean, standard deviation (SD), maximum, minimum, P25, median, and P75 will be reported. For paired measurement data, the mean difference, SD, and confidence interval (CI) will also be reported. As to enumeration data and ranked data, frequency distribution and corresponding percentage are compulsory. Baseline data of the two arms (e.g., demographic data) will undergo descriptive and inferential analyses. Intra-group efficacy comparisons before and after the treatment will be conducted by using the paired *t* test or Wilcoxon signed rank test for quantitative variables and the chi-squared test for qualitative variables. Efficacy difference between groups will be assessed with the utilization of the two-sample *t* test or corresponding non-parameter methods for quantitative variables, the chi-squared test for qualitative variables, and the Wilcoxon rank sum test for rank variables. For the primary outcome, the mean difference with two-sided 95 % CI will be reported. Statistic effectiveness is defined as the lower limit of 95 % CI above 0. Clinical effectiveness needs to be assessed after combining with clinical significance. For the consideration of the multicenter character, a covariance model is used to evaluate the center effect for the primary variable. Other secondary outcomes will take no account of the center effect. In addition, the chi-squared test will be utilized to analyze the rate of adverse events between the two arms. A table will be generated to enumerate and describe the characters of all adverse events during the study.

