The clinical trial protocol is the base of the whole study. It plays a crucial role through study preparing, proceeding, reporting, and evaluation. This protocol has been developed according to CONSORT statement [21], SPIRIT 2013 [22], and the SPIRIT 2013 explanation and elaboration: guidance for protocols of clinical trials [23] in order to establish an appropriate standard for scientific, ethical, and safety issues of the study.

In conclusion, the results of the study are expected to provide exact efficacy and safety evidence of Yirui capsules in treating hyperlipidemia. This may help provide clinicians with another option for adjunctive lipid-lowering treatments based on statins.

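### The one between-arm safety comparison named is a chi-squared test with no estimate or interval, so it cannot show how much harm is excluded.

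*Protocol article*

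**What the plan says.** The Background section of the protocol article states the aim: "we aim to demonstrate and assess the efficacy and safety of Yirui capsules in improving hyperlipidemia". The Discussion adds that "the results of the study are expected to provide exact efficacy and safety evidence of Yirui capsules in treating hyperlipidemia".

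The Statistical analysis section sets a general significance level ("the statistical significance is defined as a two-sided *P* value of <0.05") and puts safety on the same footing as efficacy for the analysis population: "All effectiveness and safety evaluations will be conducted according to the intention-to-treat (ITT) principle". For adverse events it then gives two items. The first is the between-arm comparison: "the chi-squared test will be utilized to analyze the rate of adverse events between the two arms". The second is descriptive: "A table will be generated to enumerate and describe the characters of all adverse events during the study". For count data in general it also requires frequencies and percentages: "As to enumeration data and ranked data, frequency distribution and corresponding percentage are compulsory".

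The primary outcome is treated differently. There the same section asks for a difference with a two-sided 95 % confidence interval and a decision on its limit: "Statistic effectiveness is defined as the lower limit of 95 % CI above 0". Nothing comparable is attached to adverse events.

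The Sample size calculation section bases the number of patients on the primary outcome (10 % vs 30 % reaching the LDL-C goal) and arrives at 90 per group. It says nothing about adverse event rates or about power for safety.

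**The concern.** The aim and the method do not match. A chi-squared test asks whether the data contradict equal adverse event rates. If it is significant, it points to a difference. If it is not, equal rates and a sizeable excess on Yirui may both fit the data, and the P value does not say how large an excess remains possible. A favourable safety statement needs exactly that figure.

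The trial was sized for a 20-point difference in responders, so smaller excesses in adverse events can easily go undetected. What is at stake is the safety half of the trial's question. The planned output would give percentages per arm, a P value and a listing, but no statement of the harm that the data exclude. The primary analysis is not affected.

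**Working it through.** **Inputs from the article.** 90 per arm (Sample size calculation); two-sided 0.05, chi-squared test and ITT for safety (Statistical analysis). There is no stated power for safety to reproduce.

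**Assumed inputs.** The article gives no adverse event rates, so a range of rates is used.

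**1. Power of the test.** For event counts x0 (placebo) and x1 (Yirui) out of n = 90 each, with pooled proportion q = (x0 + x1)/(2n), the uncorrected statistic is

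X² = ((x1 - x0)/n)² / [q(1 - q) × 2/n],

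and the test rejects if X² > 3.84. Exact power is the sum of the binomial probabilities of all pairs (x0, x1) that reject.

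| Placebo vs Yirui (assumed) | Power, 90 per arm | Probability of missing it |
|---|---|---|
| 5 % vs 10 % | 24 % | 76 % |
| 10 % vs 20 % | 47 % | 53 % |
| 20 % vs 30 % | 34 % | 66 % |
| 30 % vs 40 % | 29 % | 71 % |
| 15 % vs 30 % | 68 % | 32 % |
| 20 % vs 40 % | 84 % | 16 % |
| 5 % vs 20 % | 89 % | 11 % |
| 10 % vs 30 % | 93 % | 7 % |
| 15 % vs 35 % | 88 % | 12 % |

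**2. Where a doubling reaches 50 % power.** Solving for the placebo rate p at which p vs 2p has exact power 0.50 gives 10.7 % with 90 per arm, and 12.2 % if only 75 per arm contribute. Below that rate a doubling is missed more often than found. Above it the reverse holds.

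**3. What an interval would add.** Take 9/90 on placebo and 16/90 on Yirui.
- q = 25/180 = 0.139 and the difference is 7/90 = 0.0778, so X² = 0.0778² / (0.139 × 0.861 × 2/90) = 2.28 and P = 0.13.
- Wilson 95 % limits are 0.054 to 0.179 for 9/90 and 0.112 to 0.269 for 16/90.
- Newcombe lower limit: 0.0778 - √[(0.1778 - 0.1125)² + (0.1792 - 0.1000)²] = -0.025.
- Newcombe upper limit: 0.0778 + √[(0.2694 - 0.1778)² + (0.1000 - 0.0535)²] = +0.181.

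The same data give a non-significant test and an interval that leaves an excess of up to 18.1 points open. Even an observed doubling, 9/90 vs 18/90, is non-significant (X² = 3.53, P = 0.06; Newcombe -0.5 to +20.5 points).

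**4. Whether the test itself is valid for uncommon events.** With equal true rates and 90 per arm, its exact two-sided size is 0.036 at 2 %, 0.044 at 3 % and 0.042 at 5 %. It stays below the nominal 0.05.

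**The case against.** The strongest reply is that the plan contains no rule for declaring safety. The 0.05 level is general, and the only success criterion written is for the primary outcome. A reader might infer that a non-significant chi-squared test will be reported as proof of safety. The article does not say so, and that reading is not claimed here. What stands is narrower: the plan provides no figure from which a safety conclusion could properly be drawn.

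A second tempting inference is that the test would generally miss a doubling of adverse events. That depends on a rate the article does not give. All adverse events are recorded during the whole study, related or not, so the overall rate could well exceed 11 %. Power for a doubling is then above one half. Nor is the test blind to everything short of 20 % vs 40 %: 5 % vs 20 %, 10 % vs 30 % and 15 % vs 35 % all have power above 80 %, even with 72 per arm (81 %, 87 % and 81 %).

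A third is that small counts make the chi-squared test invalid. Its exact size shows no inflation, so this is no ground for complaint.

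It is also fair to say that a condensed article may leave the interval to an analysis plan that is not shown, that per-arm percentages are required and an interval could be derived from them, and that sizing a trial on efficacy alone is ordinary. All this lowers the weight of the point. It does not remove it, because the article goes beyond silence: it names a method for safety, and that method is a bare test, while the same section specifies an interval for the primary outcome. Rewording the aims in the Background or Discussion would change no analysis and is not asked for.

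**Conclusion.** The point holds as a cheap improvement. Safety is part of the stated aim, and the one between-arm comparison named for it cannot bound harm. At the assumed placebo rates of 10 %, 20 % and 30 %, a 10-point excess is missed more often than found with 90 per arm (53 %, 66 % and 71 %). For a doubling the same is true only if the placebo rate is below about 11 %. These figures rest on assumed adverse event rates, the uncorrected chi-squared test and all 90 patients per arm being analysed. The mismatch between aim and method does not depend on them.

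**What to change.** In the Statistical analysis section, replace the sentence on the chi-squared test for adverse events with wording such as: *The proportion of participants with adverse events will be reported per arm, with the risk difference (Yirui minus placebo) and its two-sided 95 % confidence interval (Newcombe score method, or an exact method for small counts). Safety will be interpreted from this interval. A P value above 0.05 will not be taken as evidence of safety.*

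The cost is a few sentences and trivial programming on data already collected, with no extra patients or procedures. The downside is that the safety statement may become less favourable, because the interval shows how much harm has not been excluded.

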### Data collection and handling of withdrawal and dropout

In this 28-week clinical trial, it is compulsory for participants to take experimental medication for a continuous 24 weeks, be present at five assessment visits, conduct several blood tests, finish certain scales, complete a diet evaluation diary card, and stop taking other lipid-lowering medication and drugs with relevant herbal ingredients. Specially assigned individuals will record the original data, and the relevant materials will be placed on file based on numerical order at the specified site appropriately. Only principal investigators and clinical investigators have the right to examine the documents. Original documents should be preserved at least 5 years after finishing the study.

For maximum compliance of patients, we require all researchers and doctors to obey the following rules. Firstly, all researchers should obey the principle of informed consent and help participants understand the requirements of the study. Secondly, researchers need to monitor the compliance of patients through the dose counting method. Thirdly, all doctors should ask patients to bring all medications to every visit to examine and record any drug combinations. Moreover, investigators will contact the participant to remind them of the visit three days in advance and to inform them of the specific arrangements for the next visit. For patients who do not respond to the medication or cannot take medication on time, increasing the frequency of the follow-up visits is compulsory.

Participants can quit the study if they experience: (1) severe adverse effect(s), (2) hypersensitivity towards the research medication, or (3) aggravation of disease. The whole research plan will be terminated for the following circumstances: (1) presence of serious adverse events related to the research medication, (2) no practical value findings of the medication during the treatment, or (3) completion of all follow-up assessments.

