**Table 1 Tab1:**
[figure not shown]
Schedule of enrollment, intervention, and assessments

There will be five visits for each participant in week 0, week 4, week 12, week 24, and week 28. At the first visit, patients will have their general data recorded and will be given the prescription. Then, patients will take the prescription to the specified pharmacy and receive either Yirui capsules or the placebo. 4 weeks and 12 weeks after the first visit, patients will come back for clinical evaluation and medication. Visit 4 is planned for the end of the treatment period (week 24); at this visit patients will only receive clinical evaluation. Afterwards, the patients will stop taking Yirui capsules or the placebo for another 4 weeks and then come back for clinical evaluation.

The study protocol was approved by the ethics committees of the First Affiliated Hospital of Jinan University, Guangdong No. 2 Provincial People’s Hospital, Hexian Memorial Affiliated Hospital of Southern Medical University, and the Fifth Affiliated Hospital, Sun Yat-sen University (Approval Version: LWXJ.YRJN-HBT-V1.0), and informed consent was obtained from each participant.

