### Outcomes

Clinical investigators will obtain written informed consent and collect basic data such as gender, age, height, weight, and medical history at baseline. For safety concerns, besides the basic data, vital signs will be taken and laboratory examinations conducted, for instance, blood pressure, heart rate, routine blood tests (e.g., red blood cell (RBC), white blood cell (WBC), hemoglobin (Hb), etc.), liver and kidney function tests (e.g., ALT, AST, CREA, etc.), pregnancy test, and 12-lead electrocardiogram (ECG). Except for the pregnancy test, which only needs to be conducted in the first visit (week 0, baseline), other tests should be conducted routinely at every visit during the treatment period (the ECG is not mandatory at the second visit (week 4)). Also, any adverse events such as abdominal discomfort should be monitored and recorded during the whole study.

Participants need to receive a blood lipid profile test which contains the following indexes: TC, TG, HDL-C, LDL-C, apolipoprotein A (apoA), apolipoprotein B (apoB), and non-high-density lipoprotein cholesterol (non-HDL-C). The blood sample should be collected after at least a 12-hour fast, and the last meal before the blood sampling should not contain greasy food. In order to evaluate the health status of participants, the MOS 36-Item Short-Form Health Survey (SF-36) is utilized [26–28]. In addition, for assessment of clinical symptoms, another symptomatic grading and quantifying scale is applied. Weight monitoring and diet evaluation are also two aspects that need to be conducted. All participants are required to complete the tests and scales mentioned above at every visit under the guidance and assistance of the clinical investigators. The results are recorded and compared within a group and between groups before and after intervention.

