Yirui capsules are designed to act as an intervention method for patients with borderline high serum lipid or an adjunctive choice for patients who could not reach the serum lipid target with conventional therapy. Based on the 2013 American College of Cardiology (ACC)/American Heart Association (AHA) guidelines on the treatment of blood cholesterol [29], the 2007 Chinese guidelines on blood lipid abnormality [30], and a previous TCM clinical trial [31], we set the treatment goal as a 30 % LDL-C decline compared with baseline after intervention. Therefore, the primary outcome is the percentage of participants who reach the goal at treatment endpoint (week 24). Secondary outcomes include the mean changes from baseline at treatment endpoint in LDL-C, TC, TG, HDL-C, apoA, apoB, non-HDL-C, SF-36 scoring, total and individual item scoring of symptomatic grading and quantifying scale, and body mass index (BMI).

Safety and tolerability assessments include collection of adverse events, physical examination, vital signs, and the relevant laboratory examination reported previously. Clinical investigators should observe any adverse events that occur during the clinical trial, including abnormal symptoms and signs, unusual laboratory indicators, etc. Whether or not the adverse event is related to the interventions, investigators are required to record it comprehensively, including onset time, related symptoms and signs, extent, duration, laboratory indexes, treatment, result, and follow-up. In addition, drug combinations should also be documented in order to analyze the correlation between adverse events and experimental products.

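### The withdrawal rule does not separate ending treatment from ending follow-up, so participants who leave early for harm or worsening would have a carried-forward rather than observed week-24 primary outcome

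*Protocol article*

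**What the plan says.** The exit rule for individual participants is in the protocol article, under Data collection and handling of withdrawal and dropout: "Participants can quit the study if they experience: (1) severe adverse effect(s), (2) hypersensitivity towards the research medication, or (3) aggravation of disease". What is left is the study; the sentence does not mention the capsules. The same section lists 24 weeks of continuous medication and attendance at five visits together as requirements of participation, and nowhere describes a participant who is off capsules but still followed.

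Four other statements bear on this:

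- Outcomes: "the primary outcome is the percentage of participants who reach the goal at treatment endpoint (week 24"), where the goal is a 30 % LDL-C decline from baseline.
- Study design, in the text with Table 1: "There will be five visits for each participant in week 0, week 4, week 12, week 24, and week 28".
- Statistical analysis: "All effectiveness and safety evaluations will be conducted according to the intention-to-treat (ITT) principle", and then "The last-observation-carried-forward method will be applied to deal with missing values".
- Outcomes, on safety: "any adverse events such as abdominal discomfort should be monitored and recorded during the whole study", and each event is to be recorded with "onset time, related symptoms and signs, extent, duration, laboratory indexes, treatment, result, and follow-up".

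The Sample size calculation section allows for about 20 % dropout, with 90 participants per group.

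**The concern.** A participant who has had a reaction to the capsules, or whose disease has worsened, can often still give a blood sample at week 24. An ITT comparison wants that value, whatever treatment the participant was taking by then. The rule as written offers leaving the study as the response to harm or worsening and says nothing about the week-24 visit for those who leave.

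The resulting gaps would not be random. Aggravation of disease may well reflect the lipid outcome itself and would be more frequent on placebo if the capsules work. Severe adverse effects and hypersensitivity depend on tolerability, which may differ between capsules and placebo. For these participants the primary comparison would rest on values carried forward from week 0, 4 or 12, although a week-24 value might have been obtainable.

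**Working it through.** **Step 1. How the rule, the visit schedule and LOCF combine.** Before week 24, lipids are measured at weeks 0, 4 and 12.

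- A participant who leaves at week 3 has only the baseline value. Carried forward, the change is 0 % and the participant is a non-responder.
- A participant who leaves after week 12 with a 30 % fall is carried forward as a week-24 responder, although off capsules for up to 12 weeks (24 − 12).

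So LOCF can err in either direction, depending on when and why people leave.

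**Step 2. The plan's dropout allowance.** The stated 90 per group is 75 × 1.20 = 90. Taking 20 % of 90 gives 18 expected dropouts per arm. (The plan's own sample size formula gives [0.10 × 0.90 + 0.30 × 0.70] / 0.20² × 10.5 = 78.75, or 79, rather than 75. That is a separate matter and is not used below.)

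**Step 3. Worst-case bound.** Suppose all 18 dropouts in each arm lack week-24 LDL-C. Compared with counting all of them as non-responders:

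- all missing active participants respond and no missing placebo participants do: +18/90 = +20 points;
- the reverse: −18/90 = −20 points.

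One participant is worth 1/90 = 1.1 points. The bound equals the planned effect of 30 % − 10 % = 20 points. However, it uses dropout from every cause, and the plan does not say what share comes from the three listed reasons.

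**Step 4. A milder illustration.** Assumptions that are not in the documents: a share s of the active arm stops early; LOCF credits these participants with the 30 % response rate; their observed week-24 rate would be the placebo rate of 10 %; the placebo arm stays at 10 %.

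Observed active rate = (1 − s) × 0.30 + s × 0.10. LOCF difference = 0.30 − 0.10 = 20 points. Overstatement = s × 0.20.

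- s = 5 %: active rate 29 %, difference 19 points, overstatement 1 point.
- s = 10 %: active rate 28 %, difference 18 points, overstatement 2 points.
- s = 20 %: active rate 26 %, difference 16 points, overstatement 4 points.

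If the same participants left before week 4 instead, LOCF would credit them with 0 %, and the difference would be understated by s × 0.10, which is 0.5 to 2 points for s from 5 to 20 %.

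**Step 5. Effect on power of using observed values.** With 90 per group, a two-sided 5 % test of two proportions (normal approximation, pooled variance under the null) has 92.5 % power for 30 % against 10 %. On the observed differences in Step 4, power is 90.2 %, 87.5 % and 80.3 % for s = 5, 10 and 20 %.

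**The case against.** The strongest reply is that the sentence is a permission. It says that participants can leave; it does not say that someone who stops capsules must leave, or that later visits are cancelled. The same section also makes more frequent follow-up visits compulsory for patients who do not respond or cannot take their medication on time. And this is a condensed article: the full protocol may describe follow-up after early stopping.

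Much of this stands, and it rules out four stronger readings that a reader might infer.

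- *Everyone who stops capsules leaves the study.* The text does not say so. It leaves open what happens to those who stop capsules without leaving.
- *Safety data after stopping are lost.* The Outcomes section points the other way: events are monitored throughout the study, and "investigators are required to record it comprehensively, including onset time, related symptoms and signs, extent, duration, laboratory indexes, treatment, result, and follow-up". Nothing says that this duty ends with the capsules.
- *ITT analysis becomes impossible.* ITT is compatible with withdrawals, and the plan names a method for missing values. Only those who leave before week 24 lack an observed value.
- *The rule costs ±20 points.* That is a generic bound for any trial of this size with 20 % dropout from all causes. It does not measure the effect of this rule.

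What does not stand is the argument that this is only missing detail. The article states an exit rule for harm and worsening and frames it as leaving the study. The provision for more frequent visits does not expressly cover permanent stopping. A reader following the text has no instruction to seek week-24 LDL-C from those who leave.

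**Conclusion.** The point holds in a limited form. The withdrawal rule merges ending treatment with ending follow-up. For participants who use it before week 24, the primary outcome would be carried forward rather than observed, for reasons related to outcome or tolerability. That fits poorly with the ITT principle and with five visits for each participant, and the passages need to be reconciled.

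The documents do not allow the size to be derived, since the share of dropout due to the three reasons is not given. The 1-to-4-point overstatement depends on an assumed stopping share and on an assumed loss of the full 20-point response advantage, and the direction could reverse if exits come early. The ±20 points is a ceiling only. The matter is worth correcting because the value in question can often still be measured, whichever imputation method is used for the rest.

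**What to change.** Reconcile the withdrawal paragraph with the visit schedule, the Outcomes section and the Statistical analysis section by stating that:

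- a participant who no longer takes capsules, for whatever reason, is asked to keep the scheduled visits, including week-24 lipids and adverse event follow-up, unless consent is withdrawn;
- withdrawal of consent is recorded separately from stopping capsules;
- the observed week-24 LDL-C, where available, is used in the ITT primary analysis, so that imputation is needed only where no value exists.

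The clinical reasons in the rule stay as they are, and no rule on when to stop treatment is proposed.

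The cost is an amendment of the protocol and consent wording, plus attendance at visits already scheduled. The article reports that recruitment was under way and that nobody had completed treatment, so at that time most week-24 values could still be collected. The statistical price is that values after stopping may dilute the on-treatment effect: in the illustration above, power falls from 92.5 % to 80.3 % if 20 % of the active arm stops. The lower figure matches the treatment difference that the ITT analysis is meant to estimate.
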